### Work-up

Pathologically documented squamous cell oro-, hypopharynx or larynx carcinomas will be sent for surgical consultation. Patients receive a complete work-up including examination under anaesthesia, head and neck CT scans, chest x-ray, abdominal ultrasound and bone scan. In case operation is either surgically or medically impossible or the patient refuses to undergo the procedure, in- and exclusion criteria will be examined and eligibility will be analyzed. Should a patient meet the trial conditions, information about participation in the study including potential risks and benefits is given to the patient. As soon as written consent is obtained, patients can be included into the trial and the required documentation will be provided by the study centre (Studienzentrale Klinische Radiologie, Abt. Strahlentherapie und Radioonkologie, [name]).

After inclusion, each patient receives a RT-planning CT-scan in an individually-adjusted precision immobilisation devices.

If a patient refuses treatment within the REACH trial, standard combined chemoradiotherapy (Carboplatin/5-FU, without cetuximab) will be offered.

### Safety and discontinuation of treatment

Toxicities are classified by type and grade due to NCI CTCAE v. 3.0, furthermore by duration, onset, and relationship to study treatment. Treatment of cetuximab-induced adverse reactions is carried according to recommendations by the manufacturer [13].

For grade 1 or grade 2 allergic reactions, a decrease of infusion rate for current and subsequent infusions is suggested. For ≥ grade 3, persistent grade 1 or grade 2 allergic reactions despite reduction of infusion rate, it is recommended to discontinue treatment with cetuximab. Skin reactions in terms of acne-like rash after cetuximab are common. For patients facing a grade 3 acne-like rash, cetuximab should be delayed for up to two subsequent infusions. Treatment also includes concomitant topical and/or oral antibiotics where necessary. Therapy can be resumed on resolution of the rash to < grade 2. Cetuximab needs to be delayed on a second or third occurrence of a grade 3 skin reaction for up to two consecutive cycles with dose reduction to 200 mg/m^2 ^or 150 mg/m^2 ^respectively. Any further occurrence of grade 3 acne-like rash will lead to discontinuation of cetuximab treatment according to the recommendations of the summary of product characteristics.

### Drug supply

#### Cetuximab (Erbitux^®^)

The monoclonal antibody cetuximab (Erbitux^®^) is provided by Merck KGaA, Darmstadt, Germany, and is stored by the University Hospital Pharmacy, Heidelberg.

The cetuximab dose applied in this setting corresponds to the recommended and approved dosage tested in combination with irinotecan in metastatic colorectal carcinoma [14]. Cetuximab is given with a loading dose of 400 mg/m^2 ^of body surface as an intravenous infusion on day 1. Subsequently, the regular weekly dose during the radiotherapy is 250 mg/m^2 ^of body surface on days 8, 15, 22, 29, 36, 43 (Figure 1). A prophylactic premedication with corticosteroids and antihistamines is required to reduce the incidence of infusion-related reactions such as allergic/hypersensitivity reactions [13].

**Figure 1 F1:**
[figure not shown]
**REACH treatment schedule: Cetuximab (Erbitux^®^) is given at a loading dose of 400 mg/m^2 ^body surface on day 1, the current dose during radiotherapy on days 8, 15, 22, 29, 36 and 43 is 250 mg/m^2 ^body surface**. Chemotherapy (Carboplatin 70 mg/m^2 ^body surface/5-FU 600 mg/m^2 ^body surface) is given on days 8-12 and 36-40. Radiotherapy (IMRT) starts one week after the loading dose of cetuximab an day 8. From day 29 onwards, an additional fraction of RT (concomitant boost) will be given to a total dose of 69,9 Gy.

#### Chemotherapy

Carboplatin will be applied at a dose of 70 mg/m^2 ^body surface as a one-hour intravenous infusion on days 8-12 and 36-40 (corresponds to RT- week 1 and week 5 of RT, Figure 1).

5-FU will be applied at a dose of 600 mg/m^2 ^of body surface as an intravenous infusion over 24 hours on days 8-12 and 36-40.

#### Radiation Therapy

Irradiation is applied as intensity-modulated radiation therapy (IMRT) using either a 6 MV linear accelerator (Siemens) with motoric multi-leaf collimator in a step and shoot technique or a helical tomotherapy machine (Tomotherapy, 6 MV). The primary tumor and cervical lymph nodes receive a dose of 50,4 Gy in daily fractions of 1.8 Gy (Monday to Friday). From study day 29 onwards, patients receive an additional fraction at 1.5 Gy per day (concomitant boost) to a total dose of 69.9 Gy (Figure 1). There is at least a 6-h interval between the two daily fractions. Isocentre and patient positioning are checked on the first fraction and then at least weekly by CT. Radiation therapy can be carried out on an out-patient basis apart from days 8-12 and 36-40 (chemotherapy), unless the patient's condition requires hospital admission.

### Target Volumes and dose prescription

The primary tumor and involved nodes - based on clinical and endoscopic findings - constitute the gross tumor volume (GTV). Nodes are considered positive if larger than 1 cm in diameter or showing a necrotic centre. The CTV contains the GTV and areas of potential microscopic spread. CTV1 consists of the primary/positive lymph nodes (GTV) and a margin of approx. 1 cm, CTV2 includes the GTV with a margin of about 2 cm as well as the lymph node areas for elective nodal irradiation. The planning target volume (PTV) also accounts for set-up variations and internal organ motion, hence the CTV is usually expanded by a margin of >0.5 cm. In cases where critical organs are directly adjacent to either GTV or CTV, margins will, of course, be adjusted. Doses are prescribed to the respective PTVs: PTVHD (consisting of CTV1 plus margin) is prescribed a total dose of 69,9 Gy whereas PTVLD (CTV2 plus margin) should receive a total dose of 50.4 Gy.

The PTVHD will at least be covered by the 95% prescription isodose; in addition, no more than 20% of the PTVHD should receive ≥ 110% and no more than 3% of any part of the PTVHD or PTVLD should receive ≤ 90% of the prescribed dose.

Doses of >110% of prescribed dose outside the target volume should be limited to <1 cm^3^.

For critical normal structures a margin of 0.5-1 cm around the spinal cord may be added to create a Planning Organ at Risk Volume (PRV). The dose to any point within the spinal cord should not exceed 45 Gy to any volume larger than 0.03 cm^3^. The maximum doses of 54 Gy to the brain stem are accepted. However, if absolutely necessary, doses of max. 60 Gy can be tolerated to brain stem volumes < 60 Gy.

The mean dose to the parotid gland should be limited to <26 Gy, alternatively at least 20 cc of the combined volume of both parotid glands to < 20 Gy or at least 50% of one gland to <30 Gy. Whenever feasible, dose to the larynx should be kept below 45 Gy.

The dose to the brachial plexus must be limited to ≤ 60 Gy in patients with suspicious level IV node(s).

Mandible: 70 Gy should not be exceeded at any point.

### Supportive Therapy

Antihistamines such as clemastine or dimentinden and steroids are administered intravenously prior to cetuximab-application. Skin reactions, especially acne-like rashes can be treated by topic or systemic antibiotics (i.e. tetracyclines, metronidazole or nadifloxacine) if necessary.

Whenever it is necessary, metoclopramide or 5-HT_3_-antagonists are used for antiemesis.

Radiation induced skin reactions are treated according to in-house protocols with mild moisturizing lotion or local application of steroids.

### Blood Samples

It is planned to collect approximately 300 ml of blood from each study subject during his/her trial participation, i.e. within a period of maximum 60 consecutive months. Potential risks of blood samplings are well predictable and include rare and mostly mild complications such as vascular injury, reversible nerve irritation and/or bleeding. Considering a potential gain of relevant information on genomic/proteomic mechanisms and predictive marker for clinical outcome in patients with advanced cancer of the head and neck, blood sample collection during the trial seems to be highly justifiable.

### Adverse events

Radiotherapy-related toxicities will be assessed using the NCI Common Toxicity Criteria (CTCAE v.3.0). Toxicity will be evaluated at baseline, weekly during radiation therapy (blood count, electrolytes, chemistry, clinical examination, patient visits) and at follow-up visits. Unacceptable toxicity is defined as unpredictable or irreversible grade 4 toxicity.

Expectable possible acute toxicities (up to 3 months after irradiation) comprise skin toxicity (desquamation, erythema, hyperpigmentation), nausea, vomiting, fatigue, weight loss, loss of appetite, pneumonitis, haematological toxicity with leucozytopenia, thrombozytopenia or anaemia. These symptoms could be treated medically and therefore usually resolve within 2-3 weeks. However, transient parenteral nutrition and hydration might be necessary in some cases. All acute toxicities should completely resolve within a few weeks post radiation therapy.

Decisions regarding cetuximab as well as chemotherapy dose adjustment will be made by using the guidelines below and are based on haematological parameters (ANC and platelets) monitored weekly during radiation before each dose of cetuximab and chemotherapy.

Expedited reporting will be carried out according to the local regulations.

### Evaluation

Local response is evaluated in accordance with the RECIST criteria (Response Evaluation Criteria in Solid Tumours) [15].

• Complete remission (CR) is defined as complete regression of the treated tumor mass (confirmation after at least 4 weeks of treatment or later)

• Partial remission (PR) is defined as reduction of sum of largest tumor diameters by at least 30%

• Stable disease (NC = no change) is defined as neither PR nor PD

• Progressive disease (PD) is defined as increase of sum of largest tumor diameters by 20%

### Sample Size Calculation

The choice of number of patients is based on pragmatic reasons. Therefore, the sample size analysis is replaced by a power analysis giving the expected accuracy of the results.

It is estimated that the two-year Local Regional Control rate will be 75 per cent. Given a constant hazard rate over time (leading to an exponential distribution), and assuming a two-year accrual time and a three-year follow-up time (leading to a median observation time of less than four years), with 60 patients treated the three-year LRC rate can be estimated with a 95%-confidence interval of approximate width of 18 per cent, i.e. if the LRC estimate is 65 per cent, the limits can be expected to be at 53 and 81 per cent.

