### Study design

The REACH study is a prospective phase II study combining the monoclonal EGF-receptor antibody cetuximab (Erbitux^®^) with standard chemotherapy and loco-regional irradiation therapy as intensity-modulated radiation therapy (IMRT) in patients with locally advanced squamous-cell carcinomas of oropharynx, hypopharynx or larynx. Patients will be treated by the Department of Radiation Oncology and Radiation Therapy, University of Heidelberg, in co-operation with the Helios Klinikum Berlin-Buch.

The primary endpoint of the study is the local-regional control (LRC).

The secondary endpoints are disease-free survival (DFS), progression-free survival (PFS), overall survival (OS), acute and late radiation effects, adverse events, proteomics and genomics.

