### Statistical Methods

The time to event for local regional control, disease-free survival, progression-free survival, overall survival will be calculated using a Kaplan-Meier estimate, along with a 95 per cent confidence interval.

Acute and late radiation effects as well as adverse events will be tabulated and listed by seriousness, severity, System Organ Class and relatedness.

Biometric analysis will be specified in more detail in the statistical analysis plan which has to be authorized before opening the database for analysis by the biometrician, the sponsor, and the LKP.

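### The stated 95% CI width for three-year LRC (18 points) contradicts the stated limits (53 and 81, 28 points apart), and 60 patients give neither: about 24 points, 53 to 77.

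*Protocol article*

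**What the plan says.** In the protocol article, Study design names the primary endpoint: "The primary endpoint of the study is the local-regional control (LRC"). The Sample Size Calculation section says that the number of patients was chosen on pragmatic grounds and that a statement of expected accuracy takes the place of a sample size calculation. Its inputs are:

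- the anticipated rate: "It is estimated that the two-year Local Regional Control rate will be 75 per cent";
- the event-time model: "Given a constant hazard rate over time (leading to an exponential distribution");
- the calendar: "assuming a two-year accrual time and a three-year follow-up time (leading to a median observation time of less than four years");
- the size: "with 60 patients treated".

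Its result is given twice, the second time as an explanation of the first: "the three-year LRC rate can be estimated with a 95%-confidence interval of approximate width of 18 per cent", and then "if the LRC estimate is 65 per cent, the limits can be expected to be at 53 and 81 per cent".

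Statistical Methods names the estimator. LRC and the survival endpoints "will be calculated using a Kaplan-Meier estimate, along with a 95 per cent confidence interval". The type of interval is not named.

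**The concern.** The two forms of the result cannot both be true: 81 − 53 = 28, not 18. The limits are also uneven about 65 (12 below, 16 above), so their midpoint is 67. Reading 18 as a half-width does not help, because 65 ± 18 is 47 to 83.

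At stake is the basis for the trial's size. The section states no hypothesis test, threshold or comparison. The rates of 75% and 65% are planning assumptions, and the interval is the only thing the section says 60 patients will deliver on the primary endpoint. A reader who relies on 18 points expects precision that the trial will not have. A reader who relies on the limits is given an upper bound of 81%, above what the stated design supports at an estimate of 65%.

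**Working it through.** **Inputs** (all from Sample Size Calculation, except the estimator, which is from Statistical Methods): n = 60; two-year LRC 75%; exponential event times; two years of accrual and three of follow-up; two-sided 95% level, z = 1.96; Kaplan-Meier estimate.

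**Step 1, the three-year rate.** Hazard = −ln(0.75)/2 = 0.1438 per year. S(3) = exp(−3 × 0.1438) = 0.75^1.5 = 0.6495. The stated 65% reproduces.

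**Step 2, censoring before year 3.** Two years of accrual plus three of follow-up gives potential observation of 3 to 5 years. Nobody is administratively censored before year 3, so Greenwood's variance reduces to the binomial one.

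**Step 3, the interval.** SE = sqrt(0.65 × 0.35 / 60) = 0.0616. Half-width = 1.96 × 0.0616 = 0.121. The interval is 52.9% to 77.1%, width 24.1 points. The lower limit of 53 reproduces; the upper limit of 81 and the width of 18 do not.

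**Step 4, other 95% methods, n = 60, estimate 65%:**

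| Method | Limits (%) | Width (points) |
|---|---|---|
| Untransformed (Greenwood/Wald) | 52.9 to 77.1 | 24.1 |
| With continuity correction | 52.1 to 77.9 | 25.8 |
| Wilson | 52.4 to 75.8 | 23.5 |
| Clopper-Pearson | 51.6 to 76.9 | 25.3 |
| Log | 54.0 to 78.3 | 24.3 |
| Log-log | 51.5 to 75.6 | 24.0 |
| Exponential model, 26.1 expected events | 53.1 to 74.5 | 21.4 |

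None gives a width of 18, and none gives 53 to 81.

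**Step 5, what the stated widths correspond to.** n = (2 × 1.96 / w)² × 0.65 × 0.35.

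- w = 0.18: n = 107.9, about 108 patients.
- w = 0.28: n = 44.6, about 45 patients.
- With 60 patients, a half-width of 9 points is 0.09/0.0616 = 1.46 standard errors, about 86% confidence.

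**Step 6, sensitivity to losses from the risk set.** The document gives no dropout rate, so these are assumptions.

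- Loss of 5% to 30% by year 3 gives widths of 24.5 to 26.6 points.
- Deaths without locoregional failure, if censored, act in the same way. The Discussion cites a three-year overall survival of 76% in a 22-patient phase II trial, a death hazard of −ln(0.76)/3 = 0.0915 per year. If half to all of those deaths occur without prior locoregional failure, the censoring hazard m is 0.046 to 0.0915. Greenwood's variance is S(3)² × [0.1438 / (60 × (0.1438 + m))] × [exp(3 × (0.1438 + m)) − 1]. This gives widths of 25.1 and 26.0 points, or limits of about 52 to 78.

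**Step 7, can one digit be corrected?** No.

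- 18 to 28: the two figures then agree, but 28 points is what about 45 patients give.
- 81 to 71: the width becomes 18, but 65 lies 12 above one limit and 6 below the other.
- 53 to 63: 65 lies 2 above one limit and 16 below the other.
- 81 to 77: the limits are then right, but the width of 18 is not.

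**The case against.** The text does not show which figure is the slip. If 18 was meant to be 28, the sentence agrees with its own limits and understates the achievable precision, so nothing is over-promised. That is a fair reading, and it means the two harms (a width that is too narrow, an upper limit that is too high) belong to different readings. It does not rescue the sentence, because under either reading the stated design does not give the stated figures.

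Uneven limits are not an error in themselves. On a log scale 53 to 81 is roughly symmetric, about sqrt(0.53 × 0.81) = 65.5%. But the log interval with 60 patients is 54.0 to 78.3. Adding deaths at the full 0.0915 per year moves it only to 53.2 to 79.3. This reading would also make the width about 28 and the stated 18 further off.

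The achievable width does depend on the method: 21 points under the exponential model, about 24 to 27 for Kaplan-Meier with 0 to 30% loss. This stands, so the method should be named. It is also true that the calculation is not shown. Uniform accrual would give a median potential observation of exactly four years, and the section says less than four, so some allowance for shortened observation cannot be ruled out. None is stated, however, and the 52 to 78 figure rests on an outside survival rate from one small trial, so it should be labelled as an assumption.

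Finally, 60 was a pragmatic choice, no decision rule hangs on the interval, and the reported interval will come from the data. This limits the consequence to the planning statement. It does not make that statement correct.

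**Conclusion.** The concern holds. The contradiction between 18 and 28 points is on the page and needs no assumption. From the section's own inputs, with the planned Kaplan-Meier estimate, an untransformed Greenwood interval and no loss before year 3, the expected 95% interval at 65% is about 53 to 77, width 24 points. Plausible changes of method or loss move the width between about 21 and 27 points, never to 18. The lower limit of 53 is right; the width of 18 and the upper limit of 81 are wrong. The stated width is about 6 points too narrow and would take about 108 patients instead of 60. The statement stands in for the sample size calculation on the primary endpoint, so it should be corrected.

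**What to change.** Recompute width and limits together, name the interval method, and replace the sentence with one such as:

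*With 60 patients, each followed for at least three years, a Kaplan-Meier estimate of 65% for three-year LRC would have a 95% confidence interval (Greenwood, untransformed) of about 53% to 77%, a width of about 24 percentage points.*

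Add that the limits widen to about 52% and 78% if patients who die without locoregional failure are censored, and state the assumed death hazard. Describe the result as a precision statement rather than a power analysis, since no hypothesis is tested.

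The cost is one sentence in the protocol, and the same sentence wherever the statistical analysis plan repeats it. The stated precision is less favourable than the published 18 points. N = 60 stays, and no extra patients are needed.

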### Statistical Methods

The time to event for local regional control, disease-free survival, progression-free survival, overall survival will be calculated using a Kaplan-Meier estimate, along with a 95 per cent confidence interval.

Acute and late radiation effects as well as adverse events will be tabulated and listed by seriousness, severity, System Organ Class and relatedness.

Biometric analysis will be specified in more detail in the statistical analysis plan which has to be authorized before opening the database for analysis by the biometrician, the sponsor, and the LKP.

## Discussion

Assuming that intensification of established chemoradiotherapy by the addition of cetuximab can further improve outcome, the primary end point of this study is local regional control. Treatment-related side effects should not be increased as compared to standard combined chemoradiotherapy. As already discussed, the combination of radiotherapy and cetuximab has shown promising results with only marginally increased toxicity or risks. In comparison with chemotherapeutic agents, treatment with EGFR inhibitors is associated with lower incidence of systemic side effects. Despite these benefits, there are some commonly occurring side effects of EGFR inhibitors (papulopustular rash, dry skin, itching, hair and periungual alterations), which can result in reduced quality of life as well as a reduction, interruption or discontinuation of cetuximab treatment. An evaluation of acute toxicity of skin and mucosa in patients with head and neck cancer receiving radiotherapy (RT) alone or in combination with radiotherapy plus chemotherapy (RCT) or with cetuximab (RIT) showed a grade 3 toxicity of the skin in 27,6% of the RIT patients (vs. 0% of RT, 7% of CRT) [16]. Typical appearance of grade 3 skin toxicity in RIT was a massive confluent desquamation of the RT field. Acute grade 3 mucositis was observed in 24,6% of RIT (vs. 12,5% of RT, 12,5% of RCT). Cetuximab associated acneiform rash grade 3 was observed in 7% of the RIT patients. Eight weeks after RT, all patients had recovered from these side effects. Cetuximab did not lead to a higher rate of RT interruptions compared to RT or RCT. Budach et al. reported on two patients with squamous-cell carcinoma of the head and neck who had severe radiation dermatitis while receiving a combination of radiotherapy and cetuximab [17]. Severe radiation dermatitis may occur after irradiation alone, but grade 4 lesions are rarely observed. Coexisting conditions like previously received chemotherapy or radiotherapy, liver or renal dysfunction with possible alterations of pharmacodynamics of cetuximab, may predispose patients to the development of more severe radiation dermatitis [17]. Another trial reported that 49% of patients treated with cetuximab and concurrent radiotherapy developed a grade III or IV radiation dermatitis [18]. Hence, the incidence of these severe skin reactions was twice as high compared to that reported by Bonner et al. [11]. To evaluate the real percentages of grade III and IV radiation dermatitis in the treatment of cetuximab with concurrent radiotherapy, a prospective, large-scaled study is needed. Currently, the exact mechanism causing these enhanced skin reactions remains to be clarified. With collecting blood samples, we try to find strategies for the identification of phenotypes and genotypes that are at risk of skin toxicities.

Chemotherapies like cisplatin or 5-FU combined with cetuximab have been used in the treatment of recurrent and/or metastatic squamous cell carcinoma of the head and neck. The results are promising and no increased or overlapping toxicity was found. In the primary treatment of locally advanced squamous cell carcinomas of head and neck, combination of chemoradiotherapy and cetuximab resulted in increased acute side effects in a phase II trial with 22 patients [6]. In the study, marked adverse events occurred, including two deaths (one pneumonia and one unknown cause), one myocardial infarction, one bacteremia, and one atrial fibrillation. With a median follow-up of 52 months, the 3-year overall survival rate was 76%, the 3-year progression-free survival rate 56%, and the 3-year locoregional control rate 71%. Despite the positive clinical results, the trial was closed prematurely. An investigation revealed no evidence that the adverse events could be attributed to the addition of cetuximab. Recently, the Radiation Therapy Oncology Group (RTOG) initiated a phase II trial [19] based on the protocol of Pfister et al. [20]. Concerning this proposed trial, no increased risk or toxicity seemed evident and therefore the benefit for the patients justifies conducting the trial. Clear instructions are defined in the protocol to ensure the safety of the patients.

Xerostomia is the most common late toxicity of radiotherapy to the head and neck. IMRT can reduce the dose delivered to the parotid glands. An analysis of Nutting et al. showed reduction of xerostomia ≥G2 (LENT-SOMA scale) at 12 and 18 months post radiation therapy from 74% (CRT) to 40% (IMRT) and 71% (CRT) and 29% (IMRT) respectively [21]. A retrospective study of Clavel et al. compared toxicity and efficacy of CRT and IMRT treated with concomitant chemotherapy (carboplatin and 5-FU) for locally advanced oropharyngeal cancer [22]. At a median follow-up of 33 months OS, DFS and LCR were significantly higher for IMRT. Additionally, patients treated with IMRT had less dermatitis and xerostomia at 24 and 36 months.
